### Planned analyses

Descriptive statistics will be derived for all predictor and outcome variables. Family socio-demographic characteristics are not expected to differ by study group, but significance tests will be conducted to confirm the success of the randomization process. Outcomes for the two study groups including infant EEG measures, stress and development, and maternal stress and depression will be compared at each measurement interval (intake, term, 4, 12, 18, and 24 months CA) using independent t-tests for differences between means for continuous data and chi-squared tests for differences between proportions for categorical data. The Bonferroni correction will be applied to account for multiple testing. Longitudinal analyses assessing differences over time will be conducted using repeated measures ANOVA for continuous data and Kruskal-Wallace or Friedman's adaptation of this test for non-parametric data. Generalized linear models will be used to assess the variability in infant development, as measured by Bayley-III Scales at 18 months CA. This variability is explained by repeated maternal and infant psychological and neurological factors after controlling for baseline family socio-demographic characteristics.

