Mothers complete initial assessments after consent and families are then assigned to the FNI intervention group or the SC group using a randomized block design. For randomization, six group assignment cards (3 FNI: 3 SC) are placed in envelopes and sealed. The envelopes are shuffled, numbered and placed in a packet prior to use. The RA withdraws an envelope from the packet to determine group assignment. Within 1 to 2 days of consenting, mothers assigned to the FNI group meet with a Nurture Specialist (NS) designated to facilitate the intervention and begin to carry this out, as described in the Intervention Methods section below. Mothers of infants assigned to the SC condition receive NICU standard care as described in the Standard Care section below. Twins are "clustered" for purposes of randomization, with both infants being assigned to the same group along with the mother.

To determine the total sample size necessary to ensure statistical power of not less than 0.8 to detect differences between group means, we considered the detectable difference for each of the primary outcome variables that would be of interest for a successful study result. Our experience and that of others suggested that effect sizes within the 'medium' range would be achievable (i.e., 0.4 to 0.6). Therefore, given the two independent samples created within the RCT design, assuming a significance level of α = .05 for a two-tailed test, we estimate that we will have at least 80% power (1-*β *≥ .80) to detect a difference between groups for effect sizes and total sample sizes as described in Table 1. Experience with the pilot study suggests that we could expect attrition at a rate as high as 40%. To accommodate this, we intend to recruit a total of N = 260 participants from which a final sample size sufficient to detect all differences of interest should be achieved.

**Table 1 T1:** Power analysis

Outcome Measure	PMA	Reference Population *μ *(*σ*)	Detectable Difference |*μ*_FN_-*μ*_SC_|	Effect Size *d*	Total N Required

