**Mother**					
**Cortisol **[**89**]	4 months	Median = 2.4	0.45	.40	186
		(IQR: 1.6-4.1)			
**CES-D **[**53**]	4 months	10.24(9.67)[90]	5.0	.52	120
		19.8 (11.1)[91]		.45	158

A power analysis was conducted to determine the sample size needed to ensure statistical power of (1-*β*) = .80.

*Non-optimal reflexes. Illustrative of the 13 NNNS subscales. Citation for the reference population is the same as that for all Outcome Measures except CES-D. Abbreviations: Bayley-III, Bayley Scales of Infant Development, III; CES-D, Center for Epidemiological Studies Depression Scale; HRV, heart rate variability; NNNS, NICU Network Neurobehavioral Scale; PMA, post-menstrual age of the infant.

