#### Psychological Assessments of FNI and SC Mothers

Mothers in both groups are assessed by means of a wide-range of psychometric instruments. As summarized in Table 2 these include indices of anxiety, depression, temperament, personality, attachment, stress, and social support, that are assessed near enrolment and before group assignment and again at Term, 4, 12, 18, and 24 months CA. Prior to randomization, mothers are administered questionnaires to assess their *levels of anxiety *(Speilberger State-Trait Anxiety Inventory, STAI [53]), and *depressive symptoms *(Center for Epidemiological Studies Depression Scale, CES-D [54]). These questionnaires must be completed by the mother before her group assignment, as her responses could be affected by the assignment itself. After group assignment, the quality of the mother's attachment is assessed using the Adult Attachment Interview (AAI) [55]). The status of inhibitory vs. approach systems (Behavioral Inhibition System-Behavioral Approach System, BIS-BAS, [56]), and Mom's Support Circle [Additional File 1] are assessed after group assignment and again at Term, 4, 12, 18, and 24 months CA. Finally, questionnaires that focus on the *mother's sense of stress *(Parenting Stress Index, PSI, infant [57,58]), availability of *social support *(Norbeck Social Support Questionnaire, NSSQ [59]), efficacy as a mother (Maternal Self-Efficacy Scale, MSES [60]), and temperament (Adult Temperament Questionnaire, ATQ [61]) are administered at the 4,12, 18, and 24 month follow-up visits.

**Table 2 T2:** Outcome measures

Parental measures	Abbreviation		Ref	Measurement	Time(s) administered
**State-Trait Anxiety Inventory**	STAI	◆	[53]	Mother's anxiety level generally and at the current moment	E1, D, T and 4, 12, 18, 24 mo. CA
**Center for Epidemiological Studies Depression Scale**	CES-D	◆	[54]	Mother's depressive symptomology during the past week	E1, D, T and 4, 12, 18, 24 mo. CA
**Behavioral Inhibition System-Behavioral Approach System**	BIS-BAS	◆	[56]	Mother's aversive and appetitive motivation	E2, T and 4, 12, 18, 24 mo. CA
**Adult Temperament Questionnaire**	ATQ	◆	[61]	Mother's temperament	4, 12, 18, 24 mo. CA
**Parenting Stress Index (short version)**	PSI	◆	[57]	Mother's parenting stress	4, 12, 18, 24 mo. CA
**Maternal Self-Efficacy Scale**	MSES	◆	[60]	Mother's feelings of effectiveness in parenting	4, 12, 18, 24 mo. CA
**Adult Attachment Interview**	AAI	◆	[55]	Mother's perception of her intimate relationships	E2

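### Follow-up CES-D and STAI are to be compared by unadjusted t-tests although both are measured before randomisation, and the groups are also tested at intake; this is valid but gives away precision

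*Protocol article*

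**What the plan says.** The section on psychological assessments of mothers has the STAI and CES-D administered before randomisation and gives the reason: "These questionnaires must be completed by the mother before her group assignment, as her responses could be affected by the assignment itself". Table 2 codes this occasion E1 (near enrolment, before assignment) and repeats both scales near discharge, at term and at 4, 12, 18 and 24 months.

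Planned analyses states that outcomes, among them maternal stress and depression, "will be compared at each measurement interval (intake, term, 4, 12, 18, and 24 months CA) using independent t-tests". No covariate is named. Intake is one of the six listed intervals, and the next sentence applies a Bonferroni correction without defining the family. The section also says, of family socio-demographic characteristics, that "significance tests will be conducted to confirm the success of the randomization process".

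Two further analyses follow. One is a repeated measures ANOVA for differences over time. The other is a generalized linear model for variability in Bayley-III at 18 months, controlling for baseline socio-demographics. Neither is said to use the E1 score as a covariate for a maternal outcome.

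**The concern.** A mother's own depression or anxiety score before assignment is likely to be among the better predictors of her later score. The protocol takes care to collect it free of any influence of allocation, and the stated group comparison then leaves it out. The price is a wider confidence interval and lower power than the same mothers could give. This matters more where the planned numbers have little slack and a multiplicity correction is to be applied.

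Testing the groups at intake is a separate weakness. For a measure completed before assignment, any difference under sound randomisation is chance. A significant result is a false positive, and a non-significant one does not show that the groups are prognostically alike. If such tests are counted in the Bonferroni divisor, they also raise the bar for the comparisons that matter.

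**Working it through.** **Inputs from the protocol**
- Test: "assuming a significance level of α = .05 for a two-tailed test"; power .80 (Table 1 footnote).
- CES-D at 4 months (Table 1): difference 5.0; SD 9.67 with total N 120, or SD 11.1 with total N 158.
- Allocation 1:1: "six group assignment cards (3 FNI: 3 SC) are placed in envelopes and sealed".
- Recruitment: "we intend to recruit a total of N = 260 participants"; "we could expect attrition at a rate as high as 40" per cent. Evaluable: 260 × 0.60 = 156, or 78 per arm.

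**Assumption.** The correlation r between E1 and follow-up CES-D is not in the protocol. The values .3, .5 and .6 are used.

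**Step 1: reproduce Table 1.** d = 5/9.67 = 0.517 and d = 5/11.1 = 0.450. A two-sample t-test (noncentral t, two-sided alpha .05, power .80) needs 60 and 79 per arm, so 120 and 158 in total. Both figures match exactly, which confirms that they rest on an unadjusted comparison.

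**Step 2: required N with the baseline score as covariate.** The residual SD is SD × √(1 − r²), so N is multiplied by (1 − r²). For SD 11.1:
- r = .3: 158 × 0.91 = 143.8, about 144
- r = .5: 158 × 0.75 = 118.5, about 119
- r = .6: 158 × 0.64 = 101.1, about 101

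**Step 3: power at 78 per arm, difference 5, SD 11.1** (noncentral t, effect size 0.4505/√(1 − r²)). The alpha of .01 is .05/5: one outcome at the five listed follow-up intervals.

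| r | effect size | power, alpha .05 | power, alpha .01 |
|---|---|---|---|
| unadjusted | 0.450 | .798 | .582 |
| .3 | 0.472 | .834 | .634 |
| .5 | 0.520 | .898 | .738 |
| .6 | 0.563 | .938 | .817 |

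**Step 4: cost of counting intake.** For one outcome, dropping intake takes the divisor from 6 to 5 and the per-test alpha from .00833 to .0100. Unadjusted power at 78 per arm goes from .557 to .582 at SD 11.1 (2.5 points) and from .710 to .732 at SD 9.67 (about 2 points).

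**Step 5: which intake nulls are true by design.** Table 2 separates E1 (before assignment) from E2 (after assignment). STAI and CES-D are E1. BIS-BAS, the AAI and Mom's Support Circle are E2, and answers given then could already reflect the allocation. The statement about true nulls therefore covers E1 measures and not every near-enrolment measure.

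**The case against.** The best defence is that nothing here is an error. An unadjusted t-test on randomised groups is unbiased and holds its type I error; chance imbalance is already allowed for in its standard error. The CES-D and STAI are secondary outcomes. The article is condensed, and covariates are often left to an analysis plan. Most of this stands, and it limits the point to precision. It does not remove the point, because the article names a specific unadjusted test and names intake as a tested interval. That is a stated choice, not an omitted detail.

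Several stronger readings are tempting but not supported:
- *Baseline goes unused except for checks.* The repeated measures ANOVA may include intake as a time point, and the Bayley-III model controls for baseline socio-demographics. Neither adjusts the visit-by-visit t-tests of maternal scores.
- *Intake tests certainly consume alpha.* The Bonferroni family is undefined. Counting intake is the natural reading of adjacent sentences but is not stated. Nothing places the socio-demographic tests in that family.
- *Adjustment rescues an underpowered CES-D comparison.* The gap is two mothers (156 against 158), and it arises only with the larger SD and attrition at its stated upper limit. At SD 9.67 the unadjusted power at 78 per arm is about .89. At alpha .01 and SD 11.1, adjustment reaches .80 only at about r = .6.
- *The same gain applies to EEG, NNNS and Bayley-III.* Table 2 lists no pre-randomisation value for them, and the protocol offers nothing from which to size a gain from gestational age.
- *The Bayley-III model gives a wrong treatment effect.* It is presented as explaining variability, not as the group comparison.

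**Conclusion.** The point holds as one of efficiency. For CES-D and STAI the stated comparison is valid but less precise than the collected data allow. For CES-D, if r lies between .3 and .6, the loss equals 9% to 36% of the required sample (1 − 0.91 to 1 − 0.64). At SD 11.1 and 78 per arm that is about 4 to 14 power points at alpha .05, or about 5 to 23 at alpha .01. These sizes rest on the assumed r, and the alpha of .01 further assumes a family of one outcome at five visits. No STAI figures can be given, because Table 1 has no STAI row.

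The intake tests are uninformative for E1 measures. Their cost in alpha is conditional on the undefined family and small beside the gain from adjustment. A reader might infer bias in the maternal results or a threat to the primary infant outcomes; the protocol supports neither. The change is worth making, but the trial's validity does not depend on it.

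**What to change.** - Analyse follow-up CES-D and STAI by ANCOVA, or by a mixed-model contrast at each visit, with the mother's E1 score on the same scale as a prespecified covariate.
- Present E1 scores and family socio-demographics descriptively by group, without significance tests.
- State the Bonferroni family and leave intake out of the count.
- Optionally, prespecify gestational age at birth as a covariate for infant outcomes, without claiming a stated gain.

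The cost is a change of wording, made before group comparisons are run. It needs no new data and no further recruitment.

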##### Twins

Twins as well as singletons are included in the study because twinning occurs commonly in the hospital where this study is being conducted, due largely to increased use of *in vitro fertilization *[51]. Twins will be "clustered" and not separated in the randomization process, since FNI cannot be delivered to only one twin. The challenges of nurturing twins in the context of the study protocol are discussed during sessions with family members and an individualized plan is developed and agreed upon. When possible, mothers will hold both twins at once. Alternatively, the father and mother will take turns holding the twins at the same time. Two follow-up assessments will be impacted; only one twin per family (the first born) will be assessed at the 4- and 12-month follow-up visits, since it was determined that the first mother-twin interaction will compromise the novelty of the second mother-twin interaction and the time required to film two twins in one day will be prohibitive. The treatment of twins in the data analysis will be based upon recognition that within the twin pair the intervention cannot be independently applied.

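### Twin pairs are randomised together, but the named tests for infant outcomes at term, 18 and 24 months have no family term, so standard errors are too small if both twins are analysed

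*Protocol article*

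**What the plan says.** All references are to the protocol article.

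- **Randomisation.** The Participants section keeps twins together, "with both infants being assigned to the same group along with the mother". The Twins section repeats this and describes twinning as common at the study hospital, without a figure.
- **Twins in the analysis.** The Twins section states: "The treatment of twins in the data analysis will be based upon recognition that within the twin pair the intervention cannot be independently applied". It names no method.
- **Which visits include both twins.** The Twins section says that "only one twin per family (the first born) will be assessed at the 4- and 12-month follow-up visits". It gives no such limit for term, 18 or 24 months.
- **Tests.** Planned analyses covers infant EEG, stress and development together with maternal outcomes at every measurement interval, "using independent t-tests for differences between means for continuous data". It adds chi-squared tests for categorical data, repeated measures ANOVA over time and a Bonferroni correction. No family effect or clustered method appears.
- **Sample size.** The Participants section computes N "given the two independent samples created within the RCT design", "assuming a significance level of α = .05 for a two-tailed test", and aims for "statistical power of not less than 0.8 to detect differences between group means". Table 1 gives total N for the infant rows as EEG 150, NNNS 96, HRV 154 and Bayley-III 174. The recruitment target of 260 is called participants here and families (130 per group) in the Abstract. Attrition may reach 40%.

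**The concern.** Two infants who share a mother, a NICU stay and the person delivering the intervention are likely to have positively correlated outcomes. Because the pair always falls in one arm, that correlation does not cancel in the group comparison; it adds to the variance of each arm's mean. A two-sample t-test on infants leaves this out, so its standard error is too small and its p-values are too low.

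The outcomes exposed include several that the article lists as primary: EEG, NNNS, Bayley-III and PLS-5. The Bonferroni correction does not repair this, because it adjusts p-values that are already too small.

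**Working it through.** **1. Does Table 1 allow for pairing?** Inputs from the Participants section and Table 1: two-sided alpha .05, power .80, 1:1 allocation. The normal approximation is total N = 4(1.96 + 0.8416)²/d² = 31.40/d², with d = difference/SD, rounded up to whole infants per arm. The last-but-one column uses the noncentral t power function.

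| Outcome | d | Normal approx. | Noncentral t | Table 1 |
|---|---|---|---|---|
| EEG | 0.2/0.434 = .461 | 148 | 150 | 150 |
| NNNS | 1.0/1.73 = .578 | 94 | 96 | 96 |
| HRV | 0.5/1.10 = .455 | 152 | 154 | 154 |
| Bayley-III | 6.0/14 = .429 | 172 | 174 | 174 |

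All four infant rows reproduce exactly for independent observations, so Table 1 contains no twin allowance.

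**2. Variance with both twins analysed.** Let n be the infants in an arm, w the share of them who belong to a complete pair, and ICC the within-pair correlation. There are nw/2 pairs, each adding a covariance of 2·ICC·σ² to the sum. Hence

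Var(mean) = (σ²/n)(1 + w·ICC), so the design effect is DE = 1 + w·ICC.

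The true standard error is √DE times the one the t-test uses. The true error rate of a nominal 5% test is 2[1 − Φ(1.96/√DE)].

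**3. Effective N after attrition.** 260 × 0.6 = 156 retained.

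- If these are infants, effective N = 156/DE.
- If these are families, they contain 156/(1 − w/2) infants, and effective N is that number divided by DE.

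The article gives neither w nor ICC. The ranges below (w .2-.5, ICC .3-.7) are assumptions.

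| w | ICC | DE | SE ratio | Type I error | Effective N, 156 infants | Infants in 156 families | Effective N, 156 families |
|---|---|---|---|---|---|---|---|
| .2 | .3 | 1.06 | 1.030 | 5.7% | 147 | 173 | 164 |
| .2 | .7 | 1.14 | 1.068 | 6.6% | 137 | 173 | 152 |
| .3 | .5 | 1.15 | 1.072 | 6.8% | 136 | 184 | 160 |
| .5 | .3 | 1.15 | 1.072 | 6.8% | 136 | 208 | 181 |
| .5 | .7 | 1.35 | 1.162 | 9.2% | 116 | 208 | 154 |

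The relative inflation grows at stricter levels. At a nominal .01, DE 1.15 gives about .016 and DE 1.35 about .027.

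**4. Power under each reading of N.** Take the middle case, w = .3 and ICC = .5.

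- If N counts infants, power at Table 1's own N falls from 80% to about 74% for EEG (150) and 75% for Bayley-III (174). The N needed for Bayley-III becomes 174 × 1.15, or 201.
- If N counts families, 156 families give an effective N of 160. Bayley-III power is then 76.7%, against 75.8% for 156 independent infants; EEG power is 82.5% against 81.6%. There is no loss.

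That 156 lies below the 174 required for Bayley-III even without twins is a separate matter.

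**The case against.** The best defence is that Planned analyses is a general paragraph covering mothers, baseline data and one-twin visits as well, while the Twins section is the specific rule and qualifies it. A t-test on family means, or on one infant per family, would satisfy both sections. The detailed clustered method could also sit in an analysis plan that is not shown. This has force: the article does not say that both twins enter as separate observations, so a reader should not infer a decision to ignore pairing. What remains is that the only tests named assume independence, are applied by name to infant EEG and development, and carry nothing over from the Twins section. Someone following that paragraph as written would run the wrong test.

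Two stronger readings are tempting but not supported:

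- **That the trial is underpowered because of twins.** This requires the 260 to be infants. The Abstract says families, and on that reading effective N is about 152-181 from 156 retained families, close to or above 156.
- **That every primary infant outcome is affected.** Infant HRV and cortisol at 4 months, listed as primary, come from a visit where only the first-born is assessed. Maternal outcomes have one mother per family. Twin clustering does not arise for either.

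**Conclusion.** The point holds for infant outcomes measurable on both twins: EEG and NNNS at term, Bayley-III at 18 months and PLS-5 at 24 months. If both twins are analysed as separate observations with the named tests, the standard error is too small for any positive within-pair correlation. Under the assumed ranges it should be about 3% to 16% larger, and the type I error is 5.7% to 9.2% rather than 5%. The upper end needs both assumptions at their maximum; the middle case is 6.8%.

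The standard-error problem does not depend on how N is counted, but the power claim does. Table 1 has no twin allowance, yet power is overstated on this account only if N counts infants, and the article is inconsistent about that.

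**What to change.** 1. In Planned analyses, for outcomes measured on both twins, replace the independent tests with a linear mixed model with a random intercept for family, or GEE clustered on family with robust standard errors. Use the clustered analogue for binary outcomes. If family means or one infant per family were intended, say so.
2. Reconcile the Abstract and the Participants section on whether 260 counts families or infants.
3. If it counts infants, apply a design effect, with a stated twin share and ICC, to the Table 1 rows for outcomes measured on both twins. Table 1 places HRV at term, while Primary and Secondary Outcome Measures places it at 4 months; only the term measurement would need the adjustment.

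The cost is revised wording and one model term, plus a short recalculation if item 3 applies. No additional data collection is needed for the analysis change.

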### Primary and Secondary Outcome Measures

The primary outcome measures assess the neurodevelopment and physiological functioning of the premature infant from birth through 24 months CA as summarized in Table 2. Primary outcome measures include: infant brain activity at term, as measured by EEG; infant neurobehavioral function from response to NNNS [62], preschool language scale [78], ASQ [68] and at 18 months CA by Bayley-III Scale [69], and the stress response at 4 months CA in infants, as measured by heart rate variability (HRV) and cortisol levels.

Our secondary outcome measures assess the co-regulation of the mother and the infant. Mother's mood, temperament and attachment will be assessed using: STAI, CES-D, BIS-BAS, ATQ, PSI, MSES, and the AAI. The infant's mood and temperament will be assessed using: BITSEA, IBQ-R, EITQ and CBCL. Mother-infant interactions and attachment will be assessed through scoring video recordings. Mother-infant stress responses will be evaluated by cortisol level assessment and autonomic function recordings (HRV, respiratory rate, body temperature). A mother's nurturing ability will be assessed by self-report and NS rating of nurturing abilities and the duration of nurturing behaviors as revealed by the Nurture Time Daily Log, the Maternal Nurture & Family Support Meeting, the Home Nurture Questionnaire and the NSSQ. An additional secondary outcome is the degree to which FNI may improve family support, which is assessed with the Mom's Support Circle worksheet. We will also collect data for an additional secondary, exploratory outcome-the effect of FNI versus SC upon peptide/cytokine/gene expression in the blood and/or breastmilk and upon the gut microbiome.

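### Table 1 promises 80% power at an unadjusted two-sided alpha of .05, but the planned analysis applies a Bonferroni correction, so that power does not hold at the Ns given

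*Protocol article*

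**What the plan says.** The sample size paragraph under Participants takes the outcomes one at a time: "we considered the detectable difference for each of the primary outcome variables". The error rate and power are fixed in the same paragraph: "assuming a significance level of α = .05 for a two-tailed test, we estimate that we will have at least 80% power". Table 1 then lists a total N per outcome, including EEG 150, NNNS 96 and Bayley-III 174. The paragraph allows for attrition of up to 40% and concludes that 260 recruits will leave enough for every difference of interest.

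Planned analyses compares the two groups on infant and maternal outcomes at six intervals, from intake to 24 months corrected age, with t-tests and chi-squared tests. The next sentence reads: "The Bonferroni correction will be applied to account for multiple testing". It does not say how many tests, or which, share the correction.

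Primary and Secondary Outcome Measures names seven primary measures: EEG, NNNS, the preschool language scale, ASQ, Bayley-III, infant HRV and infant cortisol. Its list opens: "Primary outcome measures include: infant brain activity at term, as measured by EEG". The footnote to Table 1 says of its single NNNS row: "Illustrative of the 13 NNNS subscales". The opening paragraph of Methods and Design is narrower. Its primary hypotheses concern EEG power and neurobehavioral function near term and at 18 months, which Table 1 represents by EEG, NNNS and Bayley-III.

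**The concern.** The article plans at one significance level and tests at a smaller one. A Bonferroni correction over m tests compares each p-value with .05/m. An N chosen to give 80% power at .05 therefore gives less than 80% whenever m is 2 or more. No choice of family in a separate analysis plan can reconcile the two statements as written, unless the family is a single test, in which case there is nothing to correct.

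What is at stake is the interpretation of a null result. A reader who trusts the 80% would take a non-significant EEG or Bayley-III comparison as fair evidence against a medium-sized effect. If the real power is nearer one half, it is not. The type I error is not at risk, because Bonferroni protects it.

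**Working it through.** **Inputs.** From the sample size paragraph: "assuming a significance level of α = .05 for a two-tailed test" and "we estimate that we will have at least 80% power". Allocation is 1:1, from the randomization method: "six group assignment cards (3 FNI: 3 SC) are placed in envelopes and sealed". From Table 1, as difference / SD and N:
- EEG: 0.2 / 0.434, N = 150
- NNNS: 1.0 / 1.73, N = 96
- Bayley-III: 6.0 / 14, N = 174

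Evaluable N after 40% attrition: 260 × 0.60 = 156.

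**Formula.** With d = difference / SD, the two-sample t statistic has noncentrality λ = d × √(N/4) and N − 2 degrees of freedom. Power is the chance that a noncentral t with this λ exceeds, in absolute value, the two-sided critical value at alpha = .05/m. Observations are treated as independent; twin clustering is not modelled.

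**Step 1: reproduce Table 1.** At m = 1 and 80% power, the formula returns 150 (EEG), 96 (NNNS), 154 (HRV), 174 (Bayley-III), and 120 and 158 (the two CES-D rows). These six match the printed Ns exactly. Bayley-III matches with 6/14 = .429, not with the printed d of .41. The seventh row, maternal cortisol at 186, does not reproduce from d = .40, which needs about 200 without any correction. No row contains an allowance for multiplicity.

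**Step 2: one row in full.** For EEG, d = 0.2/0.434 = .461 and λ = .461 × √37.5 = 2.82. The critical t at .05 is 1.976, and power is 80%. At .05/7 = .00714 the critical t is 2.728, and power is 54%.

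**Step 3: the family size is an assumption, so show the range at Table 1's own Ns.**

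| Tests in family (m) | Where m comes from | EEG, N = 150 | NNNS, N = 96 | Bayley-III, N = 174 |
|---|---|---|---|---|
| 1 | as Table 1 | 80% | 80% | 80% |
| 2 | smallest family that can be corrected | 71% | 71% | 71% |
| 3 | EEG, NNNS, Bayley-III | 66% | 65% | 66% |
| 7 | measures named as primary | 54% | 53% | 54% |
| 42 | 7 measures × 6 intervals | 32% | 31% | 32% |

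The last row is illustrative, since not every measure is taken at every interval.

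**Step 4: the Ns the trial may actually have.**

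| Evaluable N | m | EEG | NNNS | Bayley-III |
|---|---|---|---|---|
| 156 | 1 | 82% | 95% | 76% |
| 156 | 3 | 68% | 88% | 60% |
| 156 | 7 | 56% | 81% | 48% |
| 260 | 1 | 96% | 99.6% | 93% |
| 260 | 7 | 84% | 97% | 77% |

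For 80% power at m = 7, the total evaluable N would be 240 for EEG, 154 for NNNS and 276 for Bayley-III. The last exceeds the planned enrolment of 260.

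**The case against.** The strongest reply is that the article leaves the family open, that an analysis plan may define it, and that a narrow family costs much less. If the correction ran only within an outcome over its own visits, Bayley-III, given at 18 and 24 months, would have 2 tests and 71% power at Table 1's N. This stands as far as size goes: no single power figure can be called the trial's power. It does not remove the contradiction, because even 2 tests miss 80% at Table 1's Ns.

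A second reply is that Table 1's Ns are minimum requirements, while the trial recruits 260 and 40% is an upper bound for attrition. This also stands. A reader might infer that a true effect on any primary outcome is about as likely to be missed as found. The documents do not support that: with 7 tests NNNS keeps 81% at 156 evaluable, and with no attrition EEG has 84%.

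Third, part of the Bayley-III shortfall at 156 is not due to multiplicity. Power there is already 76% at .05, because 156 is below the 174 required. Only the fall from 76% to 48% comes from the correction.

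A reader might also extend the point to every instrument and visit in Table 2, or to the CES-D and cortisol rows of Table 1. The article nowhere says that all of Table 2 forms one family. CES-D is listed as a secondary outcome, and the cortisol row concerns the mother, whereas the primary measure is infant cortisol. Those rows do not bear on the power for the primary outcomes.

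**Conclusion.** The point holds. The 80% power is claimed at an alpha that the planned analysis will not use, and at Table 1's Ns every corrected family of two or more tests falls short of it. How far short depends on an unstated family size: about 71% for 2 tests, 66% for 3, 54% for 7. At the 156 evaluable implied by the article's own attrition figure, the loss under 7 tests matters for EEG (56%) and Bayley-III (48%) but not for NNNS (81%).

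The figures rest on Table 1's differences and SDs, equal groups, independent observations and a family size taken from the article's own lists. The defect is an overstated power claim and an undefined correction, not an invalid test.

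**What to change.** 1. In Planned analyses, state which tests form the corrected family: which outcomes, which score within each instrument, and which visit.
2. Replace Bonferroni with Holm. It gives the same familywise error control and never has less power, so the Bonferroni figures above are lower bounds for it.
3. In the sample size paragraph and Table 1, restate the power at the adjusted alpha and the expected evaluable N.

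One option for the family is the set of primary hypotheses in Methods and Design: EEG power at term, one named NNNS score and one named Bayley-III composite at 18 months. At alpha/3 and 156 evaluable this gives at least 68%, 88% and 60%. It does not bring EEG or Bayley-III back to 80%, but it states the power honestly. Moving the language scale, ASQ, HRV and infant cortisol outside the confirmatory family is a trade-off for the sponsor to decide, since fewer outcomes would then carry a confirmatory claim.

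The cost is wording and a recomputed table, with no new patients or procedures. The family should be fixed before any group comparison is run, so that the choice cannot be driven by the results.
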